### Procedure for unblinding if needed {17b}

No formal unblinding procedure is required because treatment allocation is known to participants and therapists, and blinded data analysts are not involved in clinical decision-making. No circumstances requiring emergency unblinding are anticipated.

## Data collection and management

### Plans for assessment and collection of outcomes {18a}

Surveys will be collected in both paper-pencil and digital form using German versions of the respective scales. After data collection, all data will be entered into the eCRF by the study staff.

#### Primary outcome

The primary outcome, somatic symptom severity, will be measured by the *Screening for Somatoform Disorders* (SOMS-7R [70, 71]), including 54 items (52 items for women, 50 items for men, 50 items for diverse gender identification) assessing the severity of diverse somatic symptoms over the last week on a scale from 0 (not at all) to 4 (very strongly). Additionally, the symptom-related impairment is assessed through three items. An intensity index is calculated as the mean over items 1–54 (range 0–4). In the main validation study with *N* = 325, the previous version SOMS-7 T demonstrated high internal consistency (*α* = 0.92*)* and sensitivity to treatment change [71]. The SOMS-7R has been validated in both clinical and non-clinical samples and is available pre-publication through the main authors, which are part of the study group.

#### Secondary outcomes

Adverse consequences of somatic symptoms will be measured by *Somatic Symptom Disorder-B Criteria Scale* (SSD-12; *α* = 0.95 [73]). The 12 items can be answered from 0 (never) to 4 (very often), resulting in a total sum score from 0 to 48. Somatic symptom coping will be assessed by the coping subscales of the *Pain Coping Questionnaire *(“Fragebogen zur Erfassung der Schmerzverarbeitung”; FESV; *α*_cognitive coping_ = 0.68–0.85, *α*_behavioral coping_ = 0.71–0.81 [75]). Each of the 24 items is scored from 1 (not true at all) to 6 (completely true) yielding a total sum score ranging from 24 to 144. Changes in depression will be assessed by the *Patient Health Questionnaire* (PHQ-9; *α* = 0.89 [74, 88]), which includes 9 items which are scored from 0 (not at all) to 3 (nearly every day) over a 2-week period, resulting in a total sum score from 0 to 27. Changes in anxiety will be measured by the *Generalized Anxiety Disorder* (GAD-7; *α* = 0.92 [76]). The 7 items are scored from 0 (not at all) to 3 (nearly every day) over a 2-week period, and the item scores are summarized to a total score ranged from 0 to 21. Health anxiety will be assessed by the *Whiteley Index* (WI; *α* = 0.80 in a sample of medical outpatients [77, 89]), which consists of 14 items with a dichotomous response format (yes = 1, no = 0). The total sum score ranges from 0 to 14. Pain-related disability will be measured by *Pain Disability Index* (PDI; *α* = 0.86 [44, 90, 91]), modified to assess disability related to PSS not limited to pain. The PDI includes 7 Items which are scored from 0 (no disability) to 10 (maximum disability), resulting in a total sum score ranging from 0 to 70. Changes in symptom related self-efficacy will be assessed by the *Pain Self-Efficacy Questionnaire* (“Fragebogen zur Erfassung der schmerzspezifischen Selbstwirksamkeit”; FESS; *α* = 0.92 [75, 92]), modified to assess self-efficacy related to PSS not limited to pain. The FESS includes 10 items which are scored from 1 (not at all true) to 6 (completely true), resulting in a total score ranging from 10 to 60. Quality of life will be measured using the *World Health Organization Quality of Life -BREF* (WHOQOL-BREF; *α* = 0.72–0.88 across domains [78]), which consists of 26 items scoring from 1 to 5 with varying verbal endpoints (e.g., 1 “not at all”’ to 5 “extremely”) over a 2-week period. Domain scores (physical health, psychological health, social relationship, environment) are calculated and transformed to a 0–100 scale. Changes in experience in social systems will be assessed by the *Experience in Personal Social Systems Questionnaire* (EXIS.pers; *α* = 0.92; [64]),consisting of 12 items which are scored from 1 (not at all) to 6 (entirely) over a 2-week period. Subscale means as well as an overall mean will be calculated.

### Plans to promote participant retention and complete follow-up {18b}

Participants will be informed about the aim and relevance of the study and the importance of completing the treatment and the follow-up survey. This is both for the quality of the study and for their personal chance of benefiting from the study. Furthermore, patients receive 20 EUR as reimbursement for completing the follow-up survey.

### Data management {19}

This trial will be performed using an eCRF. All protocol-required information collected during the trial must be entered by the investigator, or a designated member of the investigating team in the eCRF. All data entries, modifications or deletions will be recorded automatically in an electronic audit trail indicating the individual participant, the original and new values, the reason for and time and date of change, as well as the person executing the change. The system will be secured to prevent unauthorized access to the data or the system. Only people provided with a user ID and a password will be able to enter or change data. Computer hardware and software (for accessing the data) will be maintained at or made available for the site in compliance with applicable regulations. The investigator or a designated member of the investigating team, following review of the data in the eCRF, will confirm the validity of each participant’s data by electronic signature. The architecture of the computer system will be described in the data management plan. During data entry, integrity checks help to minimize entry errors. These data entry checks are based on the data validation plan, signed by the PI. The data entry system allows the trial monitors and data managers to control the entry process with the help of built-in review functions. Comments and requests can be promptly processed by the trial site. Checks for plausibility, consistency and completeness of the data will be performed during data entry. Based on these checks, queries will be produced. Any missing data or inconsistencies will be reported back to the respective site and clarified by the responsible investigator. After completion of data entry and if no further corrections are to be made in the database, the access rights will be withdrawn, and the database will be declared closed and used for statistical analysis. The storage system used during the trial and for archiving (irrespective of the type of media used) should provide for document identification, version history, search, and retrieval. The storage of the electronic data during the trial will be ensured by IZKS Mainz conforming to the legal regulations.

### Confidentiality {27}

The names and health data of the participants are subject to medical professional discretion and the regulations of the applicable laws on data protection. The names of the participants will not be disclosed to the PI. During the clinical trial, participants will be identified solely by means of an individual identification code. The trial site will maintain a personal participant identification list (participant numbers with the corresponding participant names) to enable records to be identified. Trial data (electronic and in paper form) will be handled in strictest confidence. Security procedures will be implemented to prevent disclosure of data to unauthorized people. The appropriate regulations of data protection legislation will be fulfilled in its entirety. The participant will declare in the written consent to release the investigator from the medical professional discretion to enable the attribution of the trial data in case of inspections by health authorities, audits and data monitoring by authorized sponsor representatives.

### Plans for collection, laboratory evaluation and storage of biological specimens for genetic or molecular analysis in this trial/future use {33}

Not applicable as no biological specimens will be collected.

## Statistical methods

### Statistical methods for primary and secondary outcomes {20a}

The *primary endpoint* will be analyzed with a linear mixed-effect model (LMM) including center, use of prescribed psychopharmaceutic (ATC code N06A, yes/no), use of other (non-psychopharmaceutic) medications such as analgesics or antihypertensives (yes/no), mental disorder comorbidity (yes/no), intervention, time point, and the interaction term of intervention and time point as fixed effects, as well as baseline value as a covariate. An autoregressive covariance structure will be used as the primary covariance structure, given the ordered repeated measurements and the expected decrease in correlations over time. Robustness will be assessed using alternative covariance structures. The mixed-effects model uses all available observations and provides valid inference under the missing-at-random assumption. Model assumptions will be checked by residual plots and sensitivity to handling of missing data using multiple imputation. The test used is a linear contrast between the groups at post-treatment (time as categorical variable) and uses a *t*-statistic. Treatment differences will be displayed by adjusted mean differences and 95% confidence intervals. Follow-up data will be analyzed by the LMM approach taking a different contrast. The primary analysis will be performed with the ITT-population. For sensitivity additional subpopulations will be analyzed. Descriptive statistics will also be provided over time by treatment and in total. The primary parameter will also be displayed over time by a boxplot. For sensitivity also response and remission in the SOMS-7R are analyzed. Response will be operationalized as percentage improvement relative to the respective baseline score, (≥ 50% improvement within the pathological range of the SOMS-7R + 25% within the full range [93]). Remission will be coded if patients fulfill response criteria and transition from a dysfunctional to a functional score range in the SOMS-7R. As another remission criterion, we will analyze group differences in diagnostic status (SSD criteria fulfilled) at post-treatment and follow-up. Response and remission will be analyzed within a logistic regression model for each time point with the same covariates as the primary model. Descriptive statistics (absolute and relative frequencies) by time point will also be provided. Continuous secondary outcomes will be analyzed within an analysis model analogous to the primary analysis model and descriptive statistics will be given. Variables expected to have a skewed distribution like working disability days will be analyzed by Wilcoxon Rank Sum test. Categorical outcomes will be analyzed by Χ^2^-tests and will also be displayed by absolute and relative frequencies. Exploratively, health care utilization will be analyzed descriptively at the item level and compared between treatment groups. We will descriptively analyze the extent to which iSOMA is a normal part of the daily working routine of therapists’ post-treatment with the NoMAD. We will test group differences in the type and frequency of self-reported side effects in the NEQ with Χ^2^-tests and independent *t*-test for severity ratings. Potential moderators of the change processes between treatments include (a) demographics, (b) clinical characteristics (e.g., comorbidity, baseline symptom severity, traumatic experience via the CTS), as well as (c) treatment characteristics (e.g., parallel treatments, type of referral, preferences, treatment expectations via GEEE) at baseline. Mediators will be assessed at baseline, during treatment (sessions 1, 5, 10, 15), post-treatment, follow-up. We will examine the temporal, contemporaneous, and between-subject interaction of the therapists’ warmth and competence, treatment expectations, alliance, and psychotherapy outcomes with network models. To test the mechanisms of action of the blended therapy, mediating variables (self-efficacy, disability, and treatment agency) will be analyzed with structural equation modelling (SEM), assuming a lagged effect of a respective mediator on the primary outcome (dual simplex model [94]). This way, indirect effects via different pathways leading to the outcome can be examined. Model fit will be evaluated. Exploratory analyzes will examine further effect-modulating variables (e.g., treatment preferences, patient-, clinical, or treatment characteristics) as moderators (i.e., interaction effects with treatment group) or in the form of subpopulation/sensitivity analyzes (e.g., comorbidity status, treatment length, health care utilization) using the same LMMs as for the main analysis.

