Session 17–19	Stress management, education on transactional stress model, stress-coping, communication skills	Solving problems and strengthening relationships
Session 20	Summary and self-management	Fit for the future

*Intervention group (blended psychotherapy):* In addition to the face-to-face treatment protocol, participants receive the accompanying internet intervention (iSOMA), consisting of seven modules and a technical introduction. Thus, iSOMA mirrors a chronological, mostly standardized self-help intervention. The content and scheduling of the iSOMA modules are tailored to the face-to-face session protocol and show a high degree of content overlap, reinforcing treatment transfer and multimodal learning (see Table 1). Each of the iSOMA modules includes standardized elements of psychoeducation, exercises, behavioral experiments, and assignments, which are presented in a multimedia format via text, audio, or video in an interactive form (e.g., free text fields for personal experience, preset feedback for multiple-choice questions, quizzes). Fictional patient examples (e.g., gastrointestinal, pain-related symptomatology, avoidant or endurance type) are used to illustrate typical problems and therapeutic principles. In addition, persuasive design features such as automatic reminders, tailored progress tracking and aspects of gamification (e.g., achievable skills) are incorporated. The modules can serve both as primers and enhancements of face-to-face sessions and are activated consecutively by therapists within the corresponding treatment sections, thus following a semi-flexible integration mode, which for example was recently studied in outpatient psychotherapy for depression and anxiety as part of the PSYCHOnlineTHERAPIE trial [56]. The ratio of treatment sessions to digital modules is approximately 3:1 (see Table 1). Patients work through the content between sessions using their own devices (e.g., PC, laptop, tablet, smartphone), while having the option to save their progress intermittently. Therapists can monitor the patient’s progress in the online modules and are encouraged to integrate content such as digital worksheets and exercises into treatment sessions. While initial contact via the platform is technically possible for therapists, it is neither intended nor permitted as part of the study protocol. According to the findings of preceding studies [57], the estimated processing time for each online-module ranges from approximately 45 to 60 min. iSOMA builds on a previously evaluated intervention form, tested as a guided, cognitive-behavioral, modular online program for PSS (non-blended). In a randomized controlled trial with 156 emerging adults (mean age 24 years, 83% female), iSOMA led to significantly greater reductions in somatic symptom severity (PHQ-15: *d* = 0.70) and SSD-related distress (SSD-12: *d* = 0.65) compared to a waitlist control group [57]. In a subsample with clinically relevant levels of self-reported somatic symptom distress (*n* = 83), similar effects than for the total sample were observed (PHQ-15: *d* = 0.68; SSD-12: *d* = 0.72). The implementation of the internet intervention utilizes the university-based, open-source eHealth platform “eSano”, which was developed by a member of the trial steering team (HB) and IT-expert (RP) [58, 59]. The platform was developed with consideration of the regulatory frameworks defined by the German Medical Devices Act and the European Union Medical Device Regulation. The software development and validation process was guided by internationally recognized standards, including IEC 62304 (classified as safety class B), GAMP5 (category 4), the FDA's General Principles of Software Validation, and the Pharmaceutical Inspection Co-operation Scheme guideline 11-3 [56].

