### Strategies to improve adherence to interventions {11c}

Both interventions are manualized, and therapists will be trained in both treatment forms. All treatments are video- (or audio-)taped and - in case of trainee therapists - continuously supervised (approximately every fourth session) by licensed supervisors experienced in the CBT rationale [51]. Licenced psychotherapists will schedule regular intervision groups. Adherence and engagement with the online modules will be automatically assessed within the platform. Therapists can monitor their patients’ platform usage (e.g., lecture/diary completion) and address potential issues in personal sessions. In the control group, patients will report their use of the self-help booklet regularly during the treatment process. Treatment integrity will be video- (or audio-)registered and rated after completion of the treatments using the method of assessing treatment delivery (MATD) in clinical trials [60]. Although therapists deliver both treatment forms, treatment contamination can practically be ruled out since therapists cannot alter the add-on (iSOMA vs. self-help booklet). Patients in the intervention group receive automatic e-mail notifications if a new module has been assigned to them or if they have not completed a module within ten days.

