
### Participant timeline {13}

Individuals expressing interest will be subjected to a telephone (or in-person) interview to determine preliminary inclusion and exclusion criteria (pre-screening), accompanied by filling out questionnaires for screening purpose (basic patient data, PHQ-15, PDI). Preliminary eligible individuals will then be invited to a personal informational interview. During the course of the interview, the participants will be provided with comprehensive information and written consent will be obtained. The diagnosis of SSD will be confirmed based on the Diagnostic Interview for Psychological Disorders (DIPS; [61]), which will be administered by independent, experienced therapists. If eligibility criteria are met and the patient agrees to participate by signing the informed consent, they will be asked to complete the baseline survey (t0). Afterwards, participants will be assigned to their study therapist and the regular, health insurance-covered therapy regimen will continue, starting with up to four probatory sessions. In the initial two probatory sessions, which are mandatory preliminary appointments in the German health care system to assess diagnosis, treatment indication, and therapeutic fit, the study therapists will continue the diagnostic process using the short form of the diagnostic interview (Mini-DIPS; [62]) to assess potential exclusion criteria (SSD not main diagnosis) or further comorbid diagnoses. Patients will be referred for routine care medical check-up (“Konsiliarbericht”) to identify medical red flags that prevent safe trial participation. In cases of uncertainty, a medical supervisor will be available for consultation regarding the clarification of potential red flags. If all inclusion criteria are fulfilled, participants will be randomly assigned to one of the two study arms automatically within the electronic database (randomization, allocation). In the third probatory session, participants in the intervention group will be granted access to iSOMA, while those in the control group will be provided with the self-help booklet. Patients will then receive 20 sessions of blended psychotherapy or enhanced psychotherapy, respectively, in accordance with the session protocol depicted in Table 1. At therapy sessions 1, 5, 10, and 15, the primary outcome and putative mediators will be assessed (paper-based or digitally). In addition, the therapists will document changes in concomitant treatments (e.g., medical treatments), SAEs/ESIs that could influence the study therapy, and actions taken (e.g., after consultation with supervisor and/or study head). At the end of treatment (after 20 sessions, regular end of therapy or discontinuation of therapy), participants will complete the post-treatment assessment (paper-based or digitally). Therapists in the blended psychotherapy condition will also complete a brief questionnaire assessing their experience with the implementation of the online platform into treatment. Patients will be invited to a diagnostic telephone interview administered by the study personnel. Six months after the end of treatment, patients will complete a follow-up survey (paper-based or digitally) and will also be invited to another diagnostic interview via telephone. Figure 2 presents the participant timeline and the scheduling of the assessments.

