## Discussion

The proposed trial aims to close a significant gap in the treatment of SSD by investigating the efficacy of a new blended psychotherapy. It is among the first trials to investigate outpatient psychotherapy for this diagnosis, which is still not implemented in the German health care system. This approach integrates a modular internet-based intervention into outpatient CBT and will be one of the first to systematically assess a manualized CBT approach for SSD. Thus, the trial directly addresses the limited availability of effective treatment options for this highly prevalent disorder [98]. The multicenter implementation across outpatient treatment centers throughout Germany ensures broad service coverage, thereby strengthening the transferability of the results to clinical practice. Compared to “passive” bibliotherapy, the add-on internet intervention will provide a range of interactive and tailored therapeutic content, multimedia features (e.g., videos, interactive exercises) as well as persuasive design features (e.g., progress bar, skill collection as achievements, lesson reminders). Together, these features of rather “active” self-help aim to promote patient engagement, encourage the integration of adaptive health behaviors into daily life, and enhance self-efficacy in coping with symptoms, which are key mechanisms of therapeutic change [41, 50]. Evidence indicates a dose-response relationship for psychotherapy of SSD [37], which is why additional online therapeutic elements could intensify and condense psychotherapy [99] without proportionally increasing therapeutic resources and costs in the same way as additional on-site sessions, making it a “smart augmentation.” Besides these add-ons, both study arms share a significant treatment component, potentially challenging expected treatment effects. Furthermore, practical challenges may arise, such as the semi-flexible integration of the internet-based intervention into manualized therapy protocols, which requires therapeutic effort in terms of planning, guidance, and monitoring. Also, while comorbid disorders are largely permitted, they will not explicitly be targeted within the scope of the intensive short-term therapy. However, the focus on SSD and the short-term nature of the treatment can foster implementability of the treatment regime.

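### The primary mixed model has no therapist term, which costs some precision and can make intervals too narrow if the arm effect differs between therapists

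*Protocol article*

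**What the plan says.** Section {20a} of the protocol article lists the terms of the primary model. Besides center, two medication indicators and mental comorbidity, it has "intervention, time point, and the interaction term of intervention and time point as fixed effects, as well as baseline value as a covariate". For the dependence between observations it states: "An autoregressive covariance structure will be used as the primary covariance structure". That structure, and the alternatives planned as robustness checks, concern the repeated measurements of one patient. No therapist effect is named, fixed or random. Continuous secondary outcomes, moderator analyses and subpopulation analyses reuse this model or a close relative ({20a}, {20b}).

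Other sections describe the therapist's place in the design:

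- After the baseline survey and before randomization, "participants will be assigned to their study therapist" (Participant timeline {13}).
- Therapists work in both arms: "Although therapists deliver both treatment forms, treatment contamination can practically be ruled out since therapists cannot alter the add-on" (Strategies to improve adherence {11c}).
- In the blended arm they activate the modules one after another, can follow progress and "are encouraged to integrate content such as digital worksheets and exercises into treatment sessions" (Intervention description {11a}).
- The Discussion lists this integration as a practical challenge, "which requires therapeutic effort in terms of planning, guidance, and monitoring".
- Randomization is stratified by center only ({16a}).

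**The concern.** Patients of one therapist share that therapist's skill, experience (licensed or in training) and way of using the add-on. The model treats them as independent once center is accounted for. Two kinds of therapist variation are therefore left out, and they act in opposite directions:

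- **Average differences between therapists.** These affect both arms alike. Ignoring them leaves their variance in the residual, and precision is lost.
- **Differences between therapists in the arm effect.** These do not cancel from the contrast. Ignoring them makes its standard error too small.

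The primary claim rests on one two-sided 5% contrast at post-treatment and its 95% confidence interval. As specified, the model cannot show which of the two kinds dominates. The remark that contamination can be ruled out does not settle this. It concerns whether patients receive the other arm's add-on, not whether outcomes under one therapist are correlated.

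**Working it through.** **1. The plan's own figure.** For d = 0.40, two-sided α = 0.05 and 80% power, the normal approximation gives 99 per arm. The exact t-test needs 100 per arm (power 80.4%; 99 per arm gives 79.97%). That makes 200 evaluable patients, and 200/(1 − 0.20) = 250. The stated figures reproduce.

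**2. Inputs.** From the article: N = 200 evaluable, 1:1 allocation, d = 0.40 in SD units, therapists crossed with arm. Not in the article, hence assumed:

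- K, the number of therapists: 20 to 100
- ρ, the share of variance due to average differences between therapists: 0 to 0.10
- s², the variance of the therapist-specific arm effects, in units of total variance: 0 to 0.10

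**3. Formulas** (balanced caseloads, one time point).

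- Variance taken by a model without therapist: 4/N = 4/200 = 0.0200, SE = 0.1414.
- True variance of the contrast: s²/K + 4(1 − ρ − s²/4)/N.
- True type I error of the model without therapist: 2[1 − Φ(1.96/R)], where R = true SE / 0.1414.
- Power when the standard error is right: Φ(0.40/SE − 1.96).

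**4. Two cases written out.**

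- Average differences only, ρ = 0.10, s² = 0: 4(0.90)/200 = 0.0180, SE = 0.1342, R = 0.949, type I error 3.9%.
- Least favorable corner, K = 20, ρ = 0, s² = 0.10: 0.10/20 + 4(0.975)/200 = 0.0050 + 0.0195 = 0.0245, SE = 0.1565, R = 1.107, type I error 7.7%.

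**5. Results over the range.**

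| K | ρ | s² | True SE | R | Type I error | Power, correct SE |
|---|---|---|---|---|---|---|
| any | 0 | 0 | 0.1414 | 1.000 | 5.0% | 81% |
| any | 0.10 | 0 | 0.1342 | 0.949 | 3.9% | 85% |
| 40 | 0.05 | 0.05 | 0.1414 | 1.000 | 5.0% | 81% |
| 24 | 0.05 | 0.05 | 0.1443 | 1.021 | 5.5% | 79% |
| 100 | 0 | 0.10 | 0.1432 | 1.012 | 5.3% | 80% |
| 24 | 0 | 0.10 | 0.1538 | 1.088 | 7.2% | 74% |
| 20 | 0 | 0.10 | 0.1565 | 1.107 | 7.7% | 72% |

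**6. Check by simulation.** The setting was eight centers as fixed effects, permuted blocks within center, no balancing by therapist, K = 24 or 48, one time point, and 6000 runs per setting. The model without therapist had a type I error of 4.9% to 5.5% with average therapist differences only, which is nominal within Monte Carlo error. With s² of 0.05 to 0.10 added, it was 5.8% to 7.0%, and the model's standard error was about 3% to 8% below the empirical one.

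**The case against.** **The statistical analysis plan may hold the term.** The article condenses a fuller document and refers to an analysis plan that is not shown. But section {20a} spells out the primary model and defers none of its terms, whereas {20c} expressly defers the details of the imputation model. This is a stated model that can be improved, not a missing detail.

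**Therapist-by-arm variation is not demonstrated.** This stands in part. CBT is manualized in both arms, training is shared, the online program is largely standardized, and therapists may not contact patients through the platform. The article says that integration takes effort, not that outcomes differ by therapist and arm. The variation is plausible, and its size is unknown.

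**The target of inference is a choice.** If the conclusion is meant for the participating therapists only, a model without a random therapist-by-arm effect is defensible. This stands, and it is why that term fits better in a sensitivity analysis than as a compulsory part of the primary model.

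**Stronger readings the article does not support.** A reader might infer that the planned intervals are simply wrong, or that the true level is near 10%. Average therapist differences alone do not raise the level, because every therapist can treat both arms. A level near 10% needs extreme inputs. With m patients per therapist per arm and an intraclass correlation r in each therapist-arm cell, the variance inflation is 1 + (m − 1)r.

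- m = 10, r = 0.05 gives 1.45 and a level of 10.4%. It implies 200/(2 × 10) = 10 therapists across eight centers.
- m = 5, r = 0.10 gives 1.40 and 9.8%. The therapist-specific effects then have an SD of √0.20 = 0.45, larger than the whole planned effect of 0.40, and about 19% of therapists would have a true effect favoring the booklet.

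A reader might also infer that 250 patients are too few. Section {14} deliberately leaves the correlation with baseline unused, while the model adjusts for baseline. With an assumed correlation of 0.5, the SE falls to 0.1414 × √0.75 = 0.1225 and power is about 90% before any therapist effect.

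**Conclusion.** The point holds in a limited form. The stated primary model omits a pre-randomization factor that groups patients by design. Omitting average therapist differences leaves type I error at about 4% to 5% and gives up some precision: modelling them yields a power of 81% to 85% on the plan's own basis. Only variation of the arm effect between therapists can make intervals too narrow. Over the whole assumed range the type I error is about 4% to 7.7%, and the true standard error is about 5% below to 11% above the reported one. A middle case (24 therapists, both variances 0.05) gives 5.5%. The 7.7% is a corner value: few therapists, no average differences between them, and the largest assumed variation in arm effect.

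These figures rest on assumed therapist numbers and variances, balanced caseloads and a single time point rather than the full repeated-measures model. They do not show that the sample size is wrong.

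**What to change.** - Add a random intercept for therapist, nested in center, to the primary model and the models built on it, with Kenward-Roger or Satterthwaite degrees of freedom. Keep the term whatever its estimate, so that the primary model does not depend on the data.
- Prespecify a sensitivity analysis that also includes a random therapist-by-intervention effect.
- Report both variance components and the therapist caseload by arm.

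The cost is a few lines in the protocol and analysis plan and a therapist identifier in the analysis data set; therapists already supply study data ({12}). The therapist variance may be estimated at zero, in which case little is gained. Intervals in the sensitivity analysis will be somewhat wider if the arm effect varies between therapists. Recruitment is planned until August 2027 and the analysts stay blinded until database lock, so the change can still be prespecified without knowledge of results. The sample size need not change on this ground.
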